### Data analysis

All analyses will be performed following the intention-to-treat principle (Schulz *et al.*, 2010). To account for missing observations in the 6-month follow-up questionnaire, multiple imputations will be conducted by applying MICE in R (Buuren and Groothuis-Oudshoorn, 2010; Blankers *et al.*, 2015).

First, descriptive analyses will be conducted to describe the sample characteristics. Second, logistic regression will be used to analyze attrition, including baseline factors and conditions as predictors. Third, if sample size allows, multilevel logistic regression analyses will be performed to assess differences between conditions in 7-day PPA, 24-hour PPA, and 3-month prolonged abstinence. Fourth, analyses of variance will be performed to test for differences in decisional conflict and appreciation of the intervention materials between conditions.

The economic evaluation will involve the performance of a combination of a cost-effectiveness analysis (CEA) and a cost–utility analysis (CUA) of data collected during the baseline and 6-month follow-up measurement (see quality of life and healthcare costs). In a CEA, the effects are presented in clinical outcomes (here additional quitters). In the CEA, the incremental cost-effectiveness ratio (ICER) will be expressed as the incremental costs per additional quitter (measured as six months PPA). The primary outcomes measure for the CUA will be QALYs, measured via EuroQol (Janssen *et al.*, 2013) and ICECAP (Al-Janabi *et al.*, 2012). The economic evaluation will be performed from a healthcare and societal perspective implying that all relevant costs and outcomes will be considered. Intervention costs, healthcare costs, patient, and family costs (in a subsample), and costs outside the healthcare sector will be assessed.

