#### Demographics, smoking characteristics, health status, and health literacy

Demographics will be assessed via age, gender (0 = male; 1 = female), nationality (0 = other nationality; 1 = Dutch nationality), education level (1 = low: no education, primary, or basic vocational school; 2 = medium: secondary vocational school or high school; 3 = high: higher vocational school or university), and occupation of the principal wage earner of the household.

Motivation to quit smoking (e.g., Bolman *et al.*, 2002; Mudde *et al.*, 2006) will be assessed via four items. Three items (e.g., ‘I am planning to quit smoking’) use 7-point Likert scales (1 = certainly not;7 = certainly yes). One item assesses whether smokers want to quit smoking including the time frame (1 = yes, within one month; 2 = yes, within three months; 3 = yes, within six months; 4 = yes, within one year; 5 = yes, but not within one year; and 6 = no, I do not plan to quit smoking).

The intention to use a specific smoking cessation method will be assessed via 20 items (e.g., ‘In order to stop smoking, I can best make use of nicotine replacement therapy’). All items use be 7-point Likert items (1 = certainly not to 7 = certainly yes). The questions were developed for this study based on the I-Change model, which aims at explaining motivational and behavioral change via integrating various social cognitive theories (De Vries, 2017).

The current use of e-cigarettes will be assessed via one item (‘Do you use e-cigarettes?’; 1 = no; 2 = yes, without nicotine; 3 = yes, with nicotine).

Cigarette dependence will be assessed via the Fagerström Test for Cigarette Dependence (Heatherton *et al.*, 1991; Fagerström, 2011). The six items of the scale will be converted into an overall score ranging from 0 to 10. The dependence level is classified as 0–2 = low; 3–4 = moderate; 5–6 = strong; and 7–10 = very strong.

The health status of the smoker (e.g., ‘Do you have type 2 diabetes?’) will be assessed for six diseases (0=‘yes’; 1=‘no’): COPD, cancer, type 2 diabetes, cardiovascular diseases, asthma, and depression (Bouwmans, 2018).

Health literacy (e.g., ‘How often do you get help with reading letters or folders of your GP, the hospital or other health care services?’) will be assessed via three items (1 = never; 5 = always) (Chew *et al.*, 2004). All variables described in this paragraph will be assessed at baseline.

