### Sample size

A power analysis for logistic regression was conducted using G * Power version 3.1 (Faul *et al.*, 2007). Considering an effect size (odds ratio) of 0.30, a power of .80, and an alpha of .05, a total sample size of 292 patients will be required. The effect size was calculated for a 10% difference between the control condition and experimental condition. Seven-day PPA was estimated to be 5% in the control condition and 15% in the experimental condition.

Assuming that patients are nested within general practices with an average cluster size of five patients, a total sample size of 300 patients will be required. Based on earlier smoking cessation studies in general practices, intra-cluster correlation (ICC) was set at .01. We will aim to recruit 60 PNs that need to recruit an average of 10 patients each. Considering a dropout rate of 50%, there will be 5 patients per GP practice that filled out the baseline questionnaire, totaling 300 patients. In order to account for drop out at six months follow-up, multiple imputations will be conducted by applying Multivariate Imputation via Chained Equations (MICE) in R (Buuren and Groothuis-Oudshoorn, 2010; Blankers *et al.*, 2015).

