### Potential limitations

First, PNs provided less smokers than expected, leading to a longer inclusion period and omission of also a 12-month follow-up as stated in our trial register, (NL7020/NTR7218). Yet, a 6-month study follow-up is still an acceptable period for assessing treatment effectiveness (West *et al.*, 2005).

Second, although we aim to include all eligible smoking patients who visit the participating general practices, there is a risk of selection bias by PNs. PNs may tend to invite more smokers who have already shown a willingness to stop smoking or who are deemed to be more easily motivated to participate, as also seen in other studies (Bundy, 2004; de Ruijter *et al.*, 2017a; 2017b). The conversational guidelines found in the intervention’s manual and flowchart handout are aimed to induce PNs to include all types of smokers.

Third, because smokers often just have one face-to-face meeting with a PN and we use mostly online questionnaires at the six months mark, we may face a high attrition rate. This is usual for studies that use online questionnaires (Eysenbach, 2005; Shahab and McEwen, 2009; Webb, 2009). We tried to overcome this by sending additional questionnaire packages so that patients could answer the questionnaire on-site if desired.

In order to try to prevent attrition at the follow-up assessment, we will also provide a shortened questionnaire including three of the aforementioned questions on abstinence (7-day PPA, 24-hour PPA, and 3-month prolonged abstinence) and one question asking the patients about EBSCIs used during their cessation attempt. This shortened questionnaire can be administered via email or telephone.

Lastly, the efficacy of counseling treatment is also dependent on contextual factors such as the patient–counselor relationship (Wampold, 2015). However, due to the nature of this study, targeting the use of evidence-based smoking cessation methods, assessing these contextual factors was beyond the scope of this study.

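### No baseline adjustment is named for the abstinence models, although unblinded practice nurses recruit patients after allocation; a short prespecified covariate set would help modestly and would only partly address selection

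*Protocol article*

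**What the plan says.** The Data analysis section describes the attrition model as "including baseline factors and conditions as predictors". The next sentence says that, if the sample is large enough, "multilevel logistic regression analyses will be performed to assess differences between conditions in 7-day PPA, 24-hour PPA, and 3-month prolonged abstinence". No covariates are named for these models, and none are ruled out. The abstract allows for covariates when appreciation and informed decision-making are compared, but describes the cessation analysis only as multilevel logistic regression.

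Under Study design, general practices are randomised 1:1 and PNs cannot be blinded. Under Recruitment of smokers, those PNs identify and invite the patients. Potential limitations concedes that "there is a risk of selection bias by PNs", in favour of smokers already willing to stop or easier to motivate. It answers this with the conversational guidelines in the manual and flowchart handout. The section on the referral aid describes the manual as going to PNs in the experimental condition.

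Likely prognostic data are collected at baseline: age, education, motivation, health status and, in the article's words, "Cigarette dependence will be assessed via the Fagerström Test for Cigarette Dependence".

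**The concern.** When practices are randomised and unblinded staff then choose whom to invite, randomisation does not balance the patients who enter. The article names a selection risk, and the described remedy reaches one arm. If it works, experimental PNs may enrol a broader and less motivated group than control PNs. If knowing their allocation makes experimental PNs favour promising patients, the difference runs the other way. A second filter follows, because the Sample size section allows for 50% loss between recruitment and the baseline questionnaire.

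At stake is the odds ratio for 7-day abstinence. The number of additional quitters in the cost-effectiveness ratio is also exposed, although the article does not say how that effect will be estimated. A covariate set fixed in advance also prevents a choice made after the results are seen.

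**Working it through.** **The plan's own figures.** Inputs from the Sample size section: "Considering an effect size (odds ratio) of 0.30, a power of .80, and an alpha of .05"; "Seven-day PPA was estimated to be 5% in the control condition and 15% in the experimental condition"; "a total sample size of 292 patients will be required"; clusters of five; ICC .01; 300 in total.

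- Odds ratio: (0.05/0.95) / (0.15/0.85) = 0.298, rounded to 0.30 (3.35 when inverted).
- Two proportions, two-sided 0.05, power 0.80: 141 per arm, 282 in total. With the rounded odds ratio of 0.30 the total is 284, against 292 stated.
- Design effect: 1 + (5 − 1) × 0.01 = 1.04, and 292 × 1.04 = 303.7, against 300 stated.
- Expected quitters: 150 × 0.05 + 150 × 0.15 = 7.5 + 22.5 = 30. If both arms quit at 5%, 15.

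The sample size reproduces closely and does not bear on this point. The count of about 30 events does, because it limits the number of covariates.

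**Effect of an arm difference.** The documents give no covariate strength and no imbalance, so both are assumed. Take one standardised covariate X with odds ratio g per SD for abstinence. Choose intercepts a0 and a1 so that the mean of expit(a + ln(g)·X) over X ~ N(0,1) is 0.05 and 0.15. Shift X by d SD in the experimental arm and recompute its rate p. The large-sample unadjusted odds ratio is [p/(1−p)] / [0.05/0.95].

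| g per SD | no effect, d = +0.3 | no effect, d = −0.3 | planned effect, d = +0.3 | planned effect, d = −0.3 |
|---|---|---|---|---|
| 1.5 | 1.13 | 0.89 | 3.78 | 2.98 |
| 2 | 1.22 | 0.82 | 4.07 | 2.76 |
| 3 | 1.35 | 0.73 | 4.45 | 2.52 |

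The planned value is 3.35. In 4,000 simulated trials per setting (150 per arm, no cluster effects), d = −0.3 cuts unadjusted power to 0.72, 0.65 and 0.55. Adjusting for X itself gives 0.81 to 0.83.

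**Balanced arms (d = 0), same simulations.**

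| g per SD | power unadjusted | power adjusted | median SE unadjusted | median SE adjusted |
|---|---|---|---|---|
| 1.5 | 0.831 | 0.835 | 0.445 | 0.450 |
| 2 | 0.838 | 0.853 | 0.443 | 0.456 |
| 3 | 0.829 | 0.874 | 0.445 | 0.476 |

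The standard error of the log odds ratio rises slightly. Power still rises because the conditional odds ratio, exp(a1 − a0), exceeds 3.35: it is 3.41, 3.53 and 3.85. For g = 2, ln(3.53)/0.456 = 2.77 against ln(3.35)/0.443 = 2.73. A separate check with three covariates and balanced arms gave power of .82–.83 unadjusted and .83–.85 adjusted, with error at or below .05.

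**How much selection adjustment removes.** Suppose there is no treatment effect, the arms differ by 0.4 SD in motivation, g = 2, and the model adjusts for a covariate correlated r with motivation but not for motivation. The unadjusted odds ratio is 1.309. The adjusted value is 1.295 at r = 0.2 and 1.225 at r = 0.5, and it reaches 1 only at r = 1. On the log scale the share removed is 1 − ln(1.295)/ln(1.309) = 4% and 1 − ln(1.225)/ln(1.309) = 25%.

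**The case against.** The strongest objection is that the point rests on silence. The sentence on the abstinence models states a purpose, not a list of terms, and a condensed article may leave covariates to a fuller document. The section is visibly condensed: the abstract's analysis of (co)variance appears there as analysis of variance. This stands. A reader might infer that the primary model is declared unadjusted, but the article does not say so.

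Second, selection that acts equally in both arms limits generalisability without biasing the odds ratio, and the article does not say that selection differs by arm. This also stands. What the article supplies is a mechanism: unblinded recruiters after allocation, and a remedy described for one arm. That makes a difference plausible without showing one.

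Third, the admitted selection is on willingness to quit, which age, education and dependence capture only in part. A reader might infer that adjustment would bring the odds ratio back to its true value. That happens only if the arms differ on the very covariate adjusted for.

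Fourth, a reader might infer that leaving out covariates costs precision. For a logistic odds ratio it does not; the cost is a little power.

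**Conclusion.** The point holds in limited form. The article names baseline predictors for attrition and none for abstinence, in a design where case mix can differ by arm in either direction and where usable covariates are already collected. Prespecifying a short adjustment set is a worthwhile improvement; its absence from the article does not invalidate the analysis.

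The expected gain is about 1 to 3 points of power with balanced arms (0 to 5 over the full assumed range), plus removal of whatever part of an arm difference the chosen covariates capture. Selection on motivation would stay largely unadjusted: only some 4% to 25% of the log odds ratio bias goes at the assumed correlations of 0.2 to 0.5.

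These sizes rest on assumed covariate strengths, imbalances and correlations, and on simulations without cluster effects. The structural part rests on the article alone.

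**What to change.** State the primary model as multilevel logistic regression of 7-day abstinence on condition, adjusted for age, education and Fagerström score, one term each. Use the same set for 24-hour and 3-month prolonged abstinence. Report the unadjusted odds ratio and the standardised risk difference beside the adjusted odds ratio; the risk difference is the natural scale for additional quitters.

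Motivation should enter only a sensitivity analysis. The questionnaire is issued after the PN registers the patient and may be completed straight after the consultation, so motivation may already reflect the intervention. Report that model with this caveat, and list residual selection on motivation as a limitation.

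The cost is a few sentences in the analysis section, with no new data and no questionnaire change. There are two small drawbacks. The adjusted odds ratio is conditional and so not directly comparable with the planned 3.35. With about 30 expected events, the covariate set has to stay this short.

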In order to expedite the use of EBSCIs in primary care and to thereby increase the number of successful quit attempts, a referral aid was developed. This aid aims to optimize the referral to and use of EBSCIs in primary care and to increase adherence to Dutch guidelines for smoking cessation. This paper aims to describe the development of the referral aid, as well as the design of the associated effectiveness and cost-effectiveness studies.

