### Study design

The aim is to conduct a multi-site two-group parallel randomized controlled trial involving an experimental condition and a control condition. Patients in the control condition will receive care as usual, which usually includes at least a mandatory brief smoking cessation advice and can be supplemented with counseling based on an evidence-based health counseling protocol similar to 5-A’s(Ask, Advise, Assess, Assist, and Arrange) Tobacco Cessation Guideline (Fiore *et al.*, 2000) as also described in the Dutch guidelines for smoking cessation (Chavannes *et al.*, 2017) and previous studies in the GP setting (Pieterse *et al.*, 2001; de Ruijter *et al.*, 2016) in the way the individual PN sees fit. In addition to the usual care, patients in the experimental condition will receive guidance and referral by the PN in accordance with the referral aid in order to select an EBSCI that fits their needs and preferences, which acts as an expansion on the Assist and Arrange steps from the 5-A’s protocol (Fiore *et al.*, 2000). The chosen EBSCI can either be administered by the PN (i.e., face-to-face counseling) or coordinated by the PN (e.g., eHealth, telephone counseling).

Randomization will occur on a practice level to prevent bias between the PN level or the patients level. General practices will be randomly allocated to either the control condition or the experimental condition in a 1:1 ratio. Randomization will take place via a random number generator that creates a string of numbers (1 = control condition, 2 = experimental condition), which will be allocated to general practices in order of registration. Patients are allocated based on their GP practice allocation. By allocation on the practice level, PNs cannot accidentally bias patients from the control group with information intended for the experimental group. As PNs from the experimental condition are provided with an intervention and PNs from the control condition are only asked to provide care as usual, blinding of the PNs is impossible. Patients will be semi-blinded, as they are unaware of the procedure of any other group than the one they attend.

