#### Website

The project’s website will consist of a general part and a password-protected part. PNs from both the experimental and the control conditions will be able to register new patients in the password-protected part. PNs from the experimental condition can furthermore access digital copies of the manual and other materials (e.g., the placemat, handouts, and flyer). Patients from the experimental condition can access materials delivering the same information as they receive from their PN. PNs and patients from the experimental condition can access a frequently asked questions (FAQ) page tailored to their needs. Smokers from the control condition can only access the general part of the website, which will contain general information about the project and the study

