#### Smoking cessation method chosen

Patients will be asked which EBSCIs they have used in any previous smoking cessation attempts and to grade the methods they have used on a scale ranging from 1 = very bad to 10 = very good. The following EBSCIs constitute the response options: face-to-face counseling, eHealth, telephone counseling, group counseling, pharmacotherapy, and nicotine replacement therapy. If a participant uses a smoking cessation method that is not included in the response options, it will be possible to indicate this by entering a free text. The smoking cessation method selected will be assessed at a 6-month follow-up.

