#### Appreciation of the intervention

After assessing which intervention materials have been noticed by the patients (e.g., ‘Have you seen the intervention’s poster in the waiting room of your general practice?’); (0 = yes; 1 = no), appreciation of the materials (e.g., ‘I think the StopWijzer materials are understandable’) will be assessed via four 5-point Likert items (1 = strongly disagree; 5 = strongly agree). Moreover, patients will be asked to grade the intervention materials (1 = very bad; 10 = very good) and patients and for comments and suggestions entering free text. The appreciation of the intervention will be assessed at a 6-month follow-up.

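### Decisional conflict is compared by ANOVA without a practice effect in a practice-randomised trial, and appreciation of the StopWijzer materials is tested against control patients who have largely nothing to rate

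*Protocol article*

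**What the plan says.** All locations are in the protocol article.

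- **Unit of allocation (Study design).** "Randomization will occur on a practice level to prevent bias between the PN level or the patients level". The ratio is 1:1, and each patient takes the condition of the practice: "Patients are allocated based on their GP practice allocation".
- **Nesting acknowledged (Sample size).** The size is adjusted for patients nested in practices, with five patients per practice on average and an ICC of .01 taken from earlier smoking cessation studies.
- **Analysis (Data analysis).** The three abstinence outcomes get multilevel logistic regression, provided the sample is large enough. The next sentence reads: "Fourth, analyses of variance will be performed to test for differences in decisional conflict and appreciation of the intervention materials between conditions". The Abstract makes the same split, with analysis of (co)variance for these two outcomes.
- **What is rated (Appreciation of the intervention).** Four Likert items, for example "I think the StopWijzer materials are understandable", and a grade from 1 to 10 for the materials. These follow questions on which materials the patient noticed.
- **Who receives the materials.** The manual goes to practice nurses (PNs) in the experimental condition (Intervention: the referral aid). Digital copies and the matching patient pages are for the experimental condition, while "Smokers from the control condition can only access the general part of the website" (Website). Control PNs give care as usual (Study design).
- **Missing data (Data analysis).** Every analysis is to follow intention to treat, and missing six-month answers are to be multiply imputed by chained equations (MICE).

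**The concern.** Two separate problems sit in one sentence of the analysis plan.

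**Independence.** ANOVA or ANCOVA at patient level treats patients of the same practice as independent. Patients of one practice share an allocation and usually a PN, and decisional conflict concerns a choice made with that PN. If scores correlate within practices, the standard error of the difference between conditions is too small and the test rejects too often. A covariate does not cure this. Because the article names multilevel models for abstinence and a different method for this outcome, the choice is stated and is not a detail left to an analysis plan.

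**Comparator.** The appreciation items rate the StopWijzer materials. A test between conditions needs ratings from patients who, on the article's own access rules, were mostly not given those materials. If ratings are limited to patients who noticed something, the control group becomes very small and self-selected by an event after allocation. If they are not limited, the intention-to-treat and imputation rules could fill in control ratings of materials never received.

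**Working it through.** **1. The article's own clustered sample size**

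Inputs (Sample size): unclustered total 292, average cluster size m = 5, ICC = .01.

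Design effect = 1 + (m − 1) × ICC = 1 + 4 × .01 = 1.04.

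292 × 1.04 = 303.7, against a stated 300 (60 × 5). This agrees within 3%, so the article applies a design effect of this kind when it plans the size.

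**2. Actual error of a patient-level test that ignores practice**

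For a nominal two-sided 5% test with equal clusters, actual error = 2 × [1 − Φ(1.96 / √DEFF)]. The article does not state sidedness; two-sided is assumed.

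| Patients per practice | ICC | DEFF | 1.96/√DEFF | Actual error |
|---|---|---|---|---|
| 5 | .01 (article) | 1.04 | 1.922 | 5.5% |
| 5 | .05 (assumed) | 1.20 | 1.789 | 7.4% |
| 5 | .10 (assumed) | 1.40 | 1.657 | 9.8% |
| 2.5 (assumed) | .05 (assumed) | 1.075 | 1.890 | 5.9% |
| 2.5 (assumed) | .10 (assumed) | 1.15 | 1.828 | 6.8% |

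The rows with 2.5 patients are there because the article's five per practice refers to completers of the baseline questionnaire, whereas decisional conflict is measured only at six months. They assume that half respond at six months; the article gives no such rate.

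**3. Check by simulation**

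Sixty practices, normal outcome with a random practice effect, no true difference, 6,000 replicates per setting, at ICC .01 / .05 / .10:

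- Patient-level test, five per practice: 5.3% / 7.4% / 10.3%.
- Patient-level test, unequal practice sizes (assumed negative binomial distribution with mean 5, at least one patient each): 5.9% / 9.4% / 13.2%.
- Test on practice means, over both size patterns: 4.6% to 5.4%.

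The formula and simulation agree, and an analysis that respects practice holds the 5% level.

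**4. Appreciation**

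No arithmetic applies; the sections are set side by side.

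- The items and the grade concern the StopWijzer materials (Appreciation of the intervention).
- The manual goes to experimental PNs (Intervention: the referral aid). Digital materials and protected patient pages are for the experimental condition, and control smokers reach only general information (Website).
- The ratings are nevertheless to be tested between conditions (Data analysis), under rules that keep all patients in the analysis and impute missing six-month answers.

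The first two lines leave control patients with little or nothing to rate. The third requires a rating from them.

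**The case against.** **The inflation is small on the article's own figures.** This stands: 5.5% against 5% would seldom change a conclusion. A reader might infer that the decisional conflict p-values are seriously too small, but the article gives no ICC for that outcome, so everything above 5.5% in the equal-cluster table rests on assumed values.

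**Five per practice is too many at six months.** This also stands. Decisional conflict is not in the shortened follow-up questionnaire, and the article expects high attrition (Potential limitations). Fewer respondents per practice lower the inflation. Unequal numbers raise it, and they are plausible: PNs are asked for 10–20 patients each, and some are expected to lag.

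**Control patients may have seen something.** A reader might infer that no valid control ratings can exist. The article does not go that far. It does not expressly withhold the poster or the paper flyers from control practices, control smokers can open the general part of the website, and the questions on noticed materials could act as a filter. But a glimpse of a poster is not exposure to the referral-aid content, and filtering after allocation destroys the randomised comparison.

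**Use of evidence-based cessation interventions.** The Introduction says "This aid aims to optimize the referral to and use of EBSCIs in primary care", and a reader might infer that use of these interventions goes untested between conditions. The article does not support that. Its Data analysis section is not exhaustive: the Abstract announces regression and structural equation modelling that the section omits. Silence in a condensed article is therefore not evidence of omission.

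**Conclusion.** The point holds as two faults of stated method, both confined to outcomes other than the primary one.

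- **Decisional conflict.** The named analysis does not match the unit of randomisation. The error of a nominal 5% test is about 5.5% at the article's ICC of .01 with five patients per practice. With assumed ICCs of .05 to .10 it is about 7% to 10% at five per practice and about 6% to 7% at 2.5 per practice. Under one assumed pattern of unequal practice sizes with mean 5 it is about 9% to 13%. The direction is certain if there is any positive within-practice correlation; the size is not known.
- **Appreciation.** The between-condition test has no meaningful comparator, whatever the ICC, because control patients have largely nothing to rate.

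The analysis of 7-day point prevalence abstinence is not touched by either fault.

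**What to change.** - **Decisional conflict:** replace the analysis of (co)variance, in both Data analysis and the Abstract, by a linear mixed model with condition as fixed effect and a random intercept for practice. A practice-level analysis is an acceptable alternative. Report the estimated ICC.
- **Appreciation:** remove the between-condition test. Report ratings and grades descriptively in the experimental condition, among patients who noticed the materials, and give that number. State that control ratings will not be imputed.

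**Cost:** a change of analysis wording only, since the planned questionnaires already supply the data. Intervals for decisional conflict become somewhat wider. With five per practice the standard error grows by √1.04 = 1.02 (2%) at ICC .01, and by √1.20 = 1.10 to √1.40 = 1.18 (10% to 18%) at the assumed ICCs of .05 to .10. That extra width is uncertainty the present analysis would leave out.
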